### Assessment of eligibility

2.4

Interested parents/guardians will be informed about the study procedure and complete a standardized pre-screening form. The questionnaire will be delivered in German over the software Qualtrics and assesses potential eligibility (e.g., age criteria and symptoms of ARFID). Since ARFID questionnaires are currently not validated in German and standardized screening cut offs are lacking, we translated the Nine Item Avoidant/Restrictive Food Intake disorder screen (NIAS) with the authors permission using forward-backward translation. We will define the presence of sensory sensitivity based on the NIAS scores > 9 on sensory sensitivity (35), as suggested by the English validated version, as standardized screening cut offs in Germany are lacking. If the screening suggests the presence of the inclusion criteria, we will schedule a video-based diagnostic interview. Parents and their child will be eligible if a primary diagnosis of ARFID with sensory sensitivity is confirmed according to the DSM-5-TR criteria based on the ARFID module for the Eating Disorder Examination (33). Additionally, we will conduct the Diagnostic Interview for Mental Disorders for Children and Adolescents (Kinder-DIPS) (36, 37) to assess any comorbid mental disorder and ask for any diagnosed disorders (e.g., autism). After the interview, we will ask participants to obtain a medical statement from their pediatrician to ensure that no medical reasons prohibit study participation. In case of exclusion at any stage, we support excluded participants to find an alternative treatment (e.g., by providing information about treatment options and health care service in Germany, resources for ARFID) to acknowledge and decrease family burden.

### Ethical approval and informed consent

2.5

The ethical committee of Konstanz University provided ethical approval for the study (IRB 25-2024). The diagnostician will retrieve written informed consent from all parents/legal guardians prior to the interviews.

### Intervention

2.6

We have made few adaptations from the manualized CBT-AR (14) to ensure suitability for digital delivery to parents and translated the intervention to German. The ExpeditionFood intervention consists of 12 sessions including eight self-guided sessions and four video therapy sessions with a study therapist. The self-guided sessions will be delivered to the parents/guardians and take about 30-60min each. The video therapy sessions will be conducted with both parents/guardians and the child with a duration of approximately 50min-60min. Additionally, psychoeducation materials for children will be provided for each session (e.g., brief summaries, case examples and psychoeducational stories). We will recommend that families complete one session per week resulting in a 12-week program. Parents/guardians will access the psychoeducational materials, video call sessions and questionnaires via the ehealth platform Curafida (ZTM Bad Kissingen GmbH, 2025). The platform can be accessed via a web browser or the ExpeditionFood app. Psychoeducational materials were created in the software Articulate Rise 360 (Articulate Global LLC., 2024). Additionally, patients can download additional materials, track their progress and write to the study therapist over chat. The study therapists will include a clinical psychologist (third author) and clinical psychologist in training (first author) under the supervision by the last author (a clinical psychologist with >15 years’ experience assessing and treating eating disorders).

Similar to the CBT-AR, the ExpeditionFood intervention consists of 4 stages, but it focuses only on sensory sensitivity as a proposed mechanism and not on weight gain (underweight participants are excluded). Therefore, additional weight gain sessions or sessions for other maintaining mechanisms are not needed. Secondly, to prioritize food exposure and behavioural change early in the intervention, we shortened CBT-AR stage 1 and 2 to one session each. In line with the CBT-AR, stage 1 will provide psychoeducation on ARFID, and stage 2 will provide psychoeducation on nutrition. In stage 3, families will conduct food exposures with their child—first in a learning phase (3a) and later in a repeated in a practice phase (3b). Stage 4 will address relapse prevention. **Table 1** depicts a detailed overview of the ExpeditionFood intervention.

**Table 1 T1:** Structure and content of the intervention.

Stage	Session	Format	Content	Homework
1	1	Clinican-delivered video-therapy	Psychoeducation: Symptoms of ARFID, CBT-AR treatment structure, development of individual ARFID formulation	Starting a parent-monitored food diary, adopting a regular eating schedule, establishing first small changes in eating behaviors
2	2	Self-guided session	Psychoeducation on balanced diet, risk of nutritional deficiencies, planning food exposure tasting session	Identifying underrepresentation of food groups in child’s diet, choosing foods for food exposure. Optional: Creating a reward schedule
3a	3	Clinican-delivered video-therapy	Food-Exposure tasting session	Food-Exposure tasting session and starting an exposure tracker
3a	4	Self-guided session	Additional tips for food-exposure sessions; strategies of integrating new foods (part 1)	Food-Exposure tasting session, tracking of exposure and integrations of foods
3a	5	Clinican-delivered video-therapy	Food-Exposure tasting session	Food-Exposure tasting session, tracking of exposure and integrations of foods
3a	6	Self-guided session	Food-Exposure tasting session, strategies of integrating new foods	Food-Exposure tasting session, tracking of exposure and integrations of foods
3a	7	Clinican-delivered video-therapy	Food exposure tasting session and troubleshooting of integrating new foods	Food-Exposure tasting session, tracking of exposure and integrations of foods
3b	8-11	Self-guided session and chat feedback	Food exposure tasting sessions and integration of accepted new foods	Food-Exposure tasting session, tracking of exposure and integrations of foods
4	12	Clinican-delivered video-therapy	Planning of further recovery steps; potential difficulties and relapse prevention	

ARFID, avoidant/restrictive food intake disorder. CBT-AR, Cognitive-Behavioral Therapy for Avoidant/restrictive food intake disorder.

At the beginning of each self-guided session, parents will fill out a brief questionnaire prompting them to reflect about the previous week They will have the chance to report difficulties, brainstorm potential solutions, and formulate questions for the study therapist. We will present psychoeducational materials in written formats including interactive functions (e.g., drop down menus) and engaging pictures. Psychoeducational materials are divided into subsections with a progress tracker (i.e., percentage of completion). Sections include “important” sections highlighting key aspects, “good to know” sections with additional information, and sections with relevant case examples. The intervention will encourage parents to apply the learned knowledge directly in daily life by setting concrete goals at the end of each session. Additionally, we will provide downloadable materials including a handout summary of the presented materials and homework sheets. For the homework and tracking (e.g., food diary, tracking of exposure section), parents can choose to either directly track food exposures in the platform or by filling out printable worksheets and uploading them at the end of each week.

In stage 3b, the practice phase, the study therapist will provide written feedback via chat on food exposure progress once weekly. Brief self-guided sessions will remind parents weekly of important strategies and tips without any new psychoeducational content. We will explain to parents that the chat will only be monitored in stage 3b and can otherwise only be used to upload homework assignments.

The video sessions will follow a similar structure, starting with an agenda, homework review, and troubleshooting. Afterwards, the therapist will present new psychoeducational materials or guide the family to conduct an in-session food exposure.

To support caregivers during the intervention and to decrease family burden (23, 38), we adopt the CBT-AR stance (i.e., non-blaming and empathic (12)) in all interactions, provide options for caregivers to add agenda points, such as concerns or questions, in video therapy sessions and allow for time flexibility in self-guided modules to decrease any extra stress associated with treatment.

### Assessment and data management

2.7

We will assess at screening (t0), baseline (t1), mid-intervention after completion of session 6(t2), post-intervention after completion of session 12(t3) and 4-week follow-up (t4). We will use German translations of all questionnaires. Additionally, parents/guardians will complete brief weekly measures after every session. Self-report data will be assessed via Qualtrics (i.e., for outcome measures, Qualtrics, 2025) and participants will be asked to provide only their assigned participant code when answering the questions. Only the internal study team will have access to the key file in digital password protected folder to link the participants code to the names. Additionally, the secure health platform Curafida (ZTM Bad Kissingen GmbH, 2025) will integrate the software MyMedax for content and reflection questions in self-guided sessions. We will use the secure video call software webPRAX for video call sessions (Healthy Projects GmbH, n.d.). We created a data protection policy and a register of all processing activities with the legal office of Konstanz University for this study. Moreover, a data protection and confidentiality agreement will be in place between the company of the health platform ZTM Bad Kissingen GmbH and the University of Konstanz.

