### Recruitment and sample size

2.3

Recruitment will take place in Germany, Switzerland, Austria where German is (at least one of) the officially spoken languages. We will recruit families via the study’s website, social media (e.g., Instagram, Facebook), flyers, articles in our university press, and advertisements provided to outpatient health care providers affiliated with Konstanz University.

We conducted a power analysis with G*Power (version 3.1) to estimate a sample size, and also considered the sample sizes used in previous one-arm CBT-AR trials (10, 11, 15, 34). Hence, we based our power analysis on a = 0.05 and 1-b = 0.95, and a medium-sized effect size of f = 0.6, which resulted in a sample size of n = 32. To account for an expected dropout rate of 20-30% (15), we will aim to recruit *N* = 40. However, as the primary aim is to assess overall feasibility and acceptability and our main secondary aim is to identify effect sizes for randomized control trials, we are aware that depending on dropout rates the power might not be sufficient to make conclusions about the efficacy.

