#### Feasibility and acceptability

2.8.1

We will assess feasibility via a retention rate. Rates ≥ 70% from pre- to post-assessment will be considered successful (39, 40). Another indicator will be the number of adverse events reported by the parents or child. Parents/guardians will be asked to report potential adverse events at the end of each session based on the recommendation for internet-intervention (41). Based on previous feasibility studies in children with ARFID we will consider a recruitment rate of ≥1 patient per month as feasible (11, 15). Additionally, based on similar research studies we will apply the following benchmarks enrolment (≥75% eligible participants enrol in the intervention). As an indicator of participants engagement, we will assess the number of times patients tasted new foods over the course of the intervention and how many different foods they tasted per week. Furthermore, we will report the average time needed to complete the intervention.

Additionally, we will ask parents and children at mid- and post treatment to rate the perceived feasibility of different intervention parts (e.g., weekly psychoeducational materials, video therapy sessions). These include ratings on the feasibility of time and effort needed for the intervention, understanding of the materials and satiation with technical quality of the platform on a 6-Point Likert scale (0 = completely agree to 1 = completely disagree). We will also measure parents’ acceptability of the intervention will by the Credibility/Expectancy Questionnaire (CEQ) (42) completed by parents and a single-item for the children.

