Diagnostic Interview for Mental Disorders in Children and Adolescents	(36)	Diagnosis of comorbid symptoms (DSM-5)			Criterion fulfilled yes/partially/no		x								
Children’s Depression Screeners (ChilD-S)	(46)	Depression	8		4 Point Likert scale; 0 = “agree” to 3 = “disagree”							x	x	x	x
State–Trait Anxiety Inventory—Child version trait subscale	(47)	Trait Anxiety	20		3-response scale							x	x	x	x
Generic Quality of Life Instrument for Children-Revised-	(51)	Health-related quality of life	24	Physical well-being psychological wellbeing, self-esteem, family, friends, education/school	5-point Likert scale from 0 = “never” to 4 = “always”							x	x	x	x
Working alliance inventory—short revised	(52, 53)	Therapeutic alliance	12		5-point Likert scale from 1 = “rarely” to 5 “always”			x	x	x					
Therapeutic Alliance Scales for Children	(54)	Therapeutic alliance	12	Bond/working alliance; Positive and negative aspects of the emotional bond	4-Point Likert scale from 1 = “not at all” to 4 = exactly right”								x	x	x
Additional measures															
Children Eating Disorder Examination-Questionnaire (EDE-Q8)	(55, 56)	eating disorder psychopathology	8	restraint, eating concern, weight concern, and shape concern	0–6 scale = number of days in the previous 28; or (b) “Not at all” to “Markedly, ratio scale	x						x	x	x	x
Children Eating Disorder Examination-Questionnaire Parent version (EDE-QP-parent version)	(56)	eating disorder psychopathology	28	restraint, eating concern, weight concern, and shape concern	0–6 scale = number of days in the previous 28; or (b) “Not at all” to “Markedly, ratio scale	x									
The Affinity for Technology Interaction (ATI) Scale	(57)	Affinity for Technology Interaction	9		6-point Likert scale, 1 = “strongly disagree” to 6 = “strongly agree”		x								

ARFID, avoidant/restrictive food intake disorder. Assessment will take place at screening (t0), baseline (t1), mid-intervention (t2), post-intervention (t3) and 4-week follow-up (t4). Additionally, parents will be asked to fill out weekly the FNS; NIAS, and adverse event scale. Furthermore, number of integrated new foods will be tracked by caregivers from week 3 onwards. Demographic characteristics (e.g., gender, age) will be assessed at screening and baseline and parent-child interaction regarding food at pre-, mid and post-treatment.

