### Proposed statistical analysis

2.10

As our primary aim is to assess feasibility, we will report recruitment rates and retention rates and number of adverse events until post-assessment with descriptive statistics. We will also report feasibility ratings of parents regarding the duration of sessions and materials, number of foods tasted per week, as well as the overall therapy duration of individuals completing the intervention. Acceptability will be descriptively reported based on parents rating on the treatment credibility (Credibility/Expectancy Questionnaire (CEQ) (48) and treatment satisfaction (Client Satisfaction Questionnaire (CSQ) (49)), as well as single-items for children.

As a secondary aim we will analyze ARFID symptoms reduction with paired sample t-test for expert-rated psychosocial impairment and sensory sensitivity (based on the Eating Disorder Examination (EDE) ARFID module, as well as self-report measures of symptoms of ARFID (i.e., Nine Item Avoidant/Restrictive Food Intake disorder screen (NIAS) (43) and Food Neophobic Scale (FNS) (44)) and children’s quality of life will be conducted from pre- to post assessments and pre-to follow-up.

Exploratory, in line with previous research we will also analyze anxiety (STAI (47)) and depression levels (Children’s Depression Screeners (46)) using dependent t-tests to test for potential changes in comorbid symptoms (12, 15).

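### Post-assessment follows session 12 with no calendar limit and change is tested by paired t-tests, so the symptom analysis covers completers only and is likely to overstate change if families who stop improve less

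*Protocol article*

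**What the plan says.** All references are to the protocol article.

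- **Timing (Assessment and data management, 2.7).** Assessments after baseline are set at "mid-intervention after completion of session 6(t2), post-intervention after completion of session 12(t3) and 4-week follow-up (t4". The trigger for t2 and t3 is a completed session, not a date.
- **Pace (Intervention, 2.6).** "We will recommend that families complete one session per week resulting in a 12-week program". The weekly rhythm is advice, and flexible timing of the self-guided modules is a stated feature.
- **Test (Proposed statistical analysis, 2.10).** "we will analyze ARFID symptoms reduction with paired sample t-test for expert-rated psychosocial impairment and sensory sensitivity". The same test is named for NIAS, FNS and quality of life, and the comparisons "will be conducted from pre- to post assessments and pre-to follow-up".
- **Sample size (Recruitment and sample size, 2.3).** The inputs are "a = 0.05 and 1-b = 0.95, and a medium-sized effect size of f = 0.6", giving 32 children, raised to 40 for an expected dropout of 20-30%. The only effect of dropout that is acknowledged is lost power.
- **Retention (Feasibility and acceptability, 2.8.1).** "We will assess feasibility via a retention rate", counted from pre- to post-assessment, with 70% or more as success.
- **Data available (Table 2 and its footnote).** The expert-rated ARFID module is scheduled at t1 and t3 only. Quality of life is child-reported at t1 to t4. NIAS and FNS are also collected at t2, and "parents will be asked to fill out weekly the FNS; NIAS, and adverse event scale". No planned test uses the t2 or weekly values.

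**The concern.** A family that stops after session 7 has, on the stated schedule, no t3. Its t4 is undefined too, since the follow-up is counted from the end of the programme. The paired t-test then drops that child altogether, including the baseline, t2 and weekly scores already collected. Who is analysed therefore depends on who finishes.

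If finishing is related to progress, the completer mean does not describe the enrolled children. That mean feeds two stated aims: proof of concept, and effect sizes for a future randomised trial. The article treats dropout as a matter of power alone, but a larger sample does not remove a selection effect.

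The same trigger affects a primary outcome. Because post-assessment follows session 12, retention coincides with finishing all 12 sessions at any speed. A slow family is neither retained nor lost on any particular date, so the comparison with 70% can depend on when it is read. The interval from t1 to t3 also differs between families.

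**Working it through.** **Step 1: reproduce the plan's figure.** Inputs from 2.3: alpha 0.05, power 0.95, effect 0.6. Exact noncentral-t power for a paired t-test, reading 0.6 as the standardised mean difference of paired scores (dz):

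- one-sided: n = 32, power 0.953, which matches;
- two-sided: n = 39, which does not match (power at 32 is 0.908).

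Dropout: 32 / (1 - 0.20) = 40, which matches. So the plan expects 40 x 0.80 = 32 children in the test, or 40 x 0.70 = 28 at 30% dropout (one-sided power 0.926). The sample size itself treats dropouts as leaving the analysis. The 70% benchmark allows the same: 0.30 x 40 = 12 children may lack t3 while retention counts as successful.

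**Step 2: size of the possible error.** Let d be the dropout proportion and k the mean change in families who stop, as a share of completers' mean change. Set completers' change at 0.60, the plan's own effect size; the ratios do not depend on this value.

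- Change in all enrolled = 0.60 x [(1 - d) + d x k]
- Completer figure / all-enrolled figure = 1 / [(1 - d) + d x k]

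The article gives d (20-30%) but nothing on k, so k is an assumption and is shown as a range.

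| k | d = 20%: all enrolled | completer figure is | d = 30%: all enrolled | completer figure is |
|---|---|---|---|---|
| 0 (no change) | 0.48 | 25% too large | 0.42 | 43% too large |
| 0.5 | 0.54 | 11% too large | 0.51 | 18% too large |
| 1 (equal) | 0.60 | correct | 0.60 | correct |
| 1.5 (improve more) | 0.66 | 9% too small | 0.69 | 13% too small |

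Example: d = 0.30, k = 0 gives 0.60 x 0.70 = 0.42 and 1 / 0.70 = 1.43. The 43% is the value at no change and not a ceiling; it would be larger if families who stop got worse.

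**Step 3: does it matter how dropout arises?** Simulation with assumed parameters, none from the article: 40 children, weekly scores, random intercept SD 1, random change over 12 sessions SD 0.85, residual SD 0.4, per-session dropout logit = -4.2 + slope x observed change, true mean change zero, two-sided paired t-test on completers.

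| Dropout mechanism | Retained | Completers' mean change | Significant |
|---|---|---|---|
| slope 2.2 | about 70% | -0.30 | about 40% |
| slope 1.1, same intercept | about 81% | -0.12 | 10% |
| slope 1.1, intercept raised to hold retention near 71% | about 71% | about -0.17 | about 15% |
| slope 0 | about 85% | 0.00 | 5% |

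The distortion is real when dropout follows progress, and vanishes when it does not.

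**Step 4: what a mixed model can repair** (same assumptions, slope 2.2, true change zero, few replicates).

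- All weekly scores, dropout driven by observed scores: mean change 0.00, significant in 3-6% of trials.
- Random-intercept model on t1, t2 and t3 only: -0.23, 41%.
- Random-intercept model on t1 and t3 only: -0.27, 42%.
- Weekly scores, but dropout driven by the underlying change: -0.20, 34%.

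The model helps mainly where weekly scores exist, which by the Table 2 footnote means parent-reported NIAS and FNS. It helps child-reported outcomes less, and the expert-rated module (t1 and t3) hardly at all.

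**The case against.** Five points can be made for the plan.

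1. **The direction of bias is not established.** Nothing in the article says how families who stop fare. They may leave because of time or burden, or because the child improved early. This stands: a reader might infer that improvement *is* overstated, and the documents support only that it is likely to be if families who stop improve less.

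2. **The schedule describes the normal course.** The article does not say that families who stop will not be contacted, and such contact may be laid down in a fuller document. This stands in part: a reader might infer that these families will definitely not be assessed, and the text does not say so. But the stated trigger for t3 is completion of session 12, the stated test needs a t3 value, and the sample size counts dropouts as lost. The point rests on those statements and not on a missing section.

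3. **A mixed model is no general cure.** Step 4 confirms this. A reader might infer that changing the model is enough; it is not, and for the expert-rated scales it is no substitute for obtaining the assessment.

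4. **Flexible pace is deliberate and duration will be reported.** True, and retention is worded as assessment to assessment and not as sessions attended. But the planned durations describe families who finish, and they do not supply a date at which a family counts as lost.

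5. **Feasibility is primary and there is no control arm.** Also true. Pre-post change is not a treatment effect under either analysis, and the article is modest about efficacy. It nevertheless makes effect sizes for the next trial an aim, and its caution concerns power, not selection.

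**Conclusion.** The structural point holds on the stated text: t3 follows session 12 without a calendar limit, families who stop have no assessment point, and paired t-tests restrict the symptom analysis to completers, with 20-30% dropout expected.

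The consequence is conditional. If families who stop improve less than completers, the change and the effect sizes are likely overstated: by 25-43% with no change in those families and by 11-18% with half the completers' change. With equal change the error is nil, and with one and a half times the completers' change the figure is 9-13% too small. These ranges rest on assumed values of k and on the article's own dropout range. The structural statement can be made with high confidence; the direction and size of the bias cannot.

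The retention benchmark has a smaller but definite defect: no date at which a slow family is counted as lost. The plan should be changed, because a t3 assessment that is never obtained cannot be recovered at analysis.

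**What to change.** 1. **Assess everyone (the leading change).** Invite every enrolled family, including those who stop, to t3 with both questionnaires and the expert-rated module, at session 12 or at a calendar limit from baseline that the investigators set in advance, whichever comes first. Place t4 four weeks later. This is the only remedy for the expert-rated scales.
2. **Use the data collected.** For parent-reported NIAS and FNS, estimate t1-t3 and t1-t4 change with 95% CI in all enrolled children by a linear mixed model on t1-t4 and weekly scores. Keep the paired t-test as a completer sensitivity analysis. Apply the same model to child-reported outcomes at t1-t4, noting that it removes less bias there. State that the model assumes dropout depends on observed scores, and add a sensitivity analysis assuming no change in families without t3.
3. **Separate two quantities.** Report retention as t3 obtained within the window, and separately the number completing 12 sessions.

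Cost: one further questionnaire invitation and interview for the 8-12 families expected to stop (20-30% of 40), plus a standard model. Some slow families will be assessed before session 12, and the estimated effect may be less favourable.
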